## Abstract

*N*-palmitoylethanolamine (PEA) plays a key role in preventing Aβ-mediated neuroinflammation and neurotoxicity in murine models. It has been demonstrated that PEA provides anti-neuroinflammatory, pain-relieving and neuroprotective actions even in humans. In this project, we aim to evaluate these anti-neuroinflammatory effects via the cognitive evaluation and biochemical analyses of a 12-month oral administration of PEA in subjects with mild cognitive impairment (MCI). Subjects with MCI will be randomized to placebo or PEA groups, and followed for another 6 months. Cognitive abilities and neurological inflammation will be examined at baseline and after treatment. The specific objectives of the project are to ascertain whether: (i) PEA influences the scores of the neuropsychological and behavioral evaluations after one-year treatment, comparing PEA-treated and placebo subjects in both MCI and control groups; (ii) PEA can change the inflammatory and neuronal damage markers of blood and urine in MCI subjects; and (iii) these changes correlate with the clinical scores of participating subjects.

## 1. Introduction

Alzheimer’s disease (AD) is the most common type of dementia; its consequences dramatically affect patients and their families’ lives [1]. The progressive population aging on a global scale will lead to an increase in the number of people affected by AD, with high costs for national healthcare systems. Therefore, an early diagnosis could be crucial for the better management of AD, and therapeutic intervention at a preclinical stage of the disease may have a better chance of postponing the patient’s loss of autonomy, with obvious consequences in economic terms as well.

Despite decades of intensive research, AD remains incurable. Current therapies mainly focus on cholinergic and N-methyl-D-aspartate receptor pathways, providing only symptomatic relief, while several drugs targeting Aβ and tau have failed in Phase III clinical trials. Thus, the identification of novel therapeutic targets in order to prevent or delay disease progression appears urgent.

It is well known that mild cognitive impairment (MCI) represents a state of transition between normal cognition and dementia, particularly AD. It is estimated that its prevalence ranges between 15% and 20% after the age of 60, with an annual conversion rate to dementia up to 15% per year [2].

In this context, it could be particularly relevant to intervene in subjects with mild cognitive impairment (MCI) through nutraceutical, non-pharmacological treatments that could help arrest/slow down conversion to AD.

Among the nutritional substances that may be used to positively affect cognitive decline in elderly, *N*-palmitoylethanolamine (PEA) appears to come to the forefront owing to its high efficacy/risk ratio and lack of both tolerance induction and interference with other conventional therapies used for counteracting mental decline. PEA is an endogenous bioactive lipid biochemically and functionally related to endocannabinoids, though it does not bind to the same receptors [3]. Similarly to its congener, *N*-arachidonoylethanolamine (or anandamide, AEA), a major endocannabinoid [4], PEA acts as local mediator and its physiological tone depends on a finely regulated balance between biosynthesis, mainly catalyzed by NAPE-selective phospholipase D (NAPE- PLD), and degradation, mainly catalyzed by fatty acid amide hydrolase (FAAH) and *N*-acylethanolamine-hydrolyzing acid amidase (NAAA) [5,6]. Within the brain, PEA is produced “on demand” by neurons, microglia and astrocytes, thus having a pleiotropic, pro-homeostatic role in neurochemical and neuroimmune responses to various injurious processes, including those associated with AD [7,8]. In this context, growing preclinical evidence in animal models of β-amyloidosis shows that PEA is efficacious in preventing neuroinflammation, cognitive deficit and Aβ-mediated neurotoxicity, likely via peroxisome proliferator-activated receptor (PPAR)-α-dependent mechanism [9,10,11]. A growing body of preclinical studies attests the anti-neuroinflammatory, pain-relieving and neuroprotective actions of micronized/ultra-micronized formulations of PEA, which favor its oral bioavailability over unprocessed PEA [12,13].

PEA appears to have a good safety profile. Unlike other endocannabinoids, only relatively inactive products such as palmitic acid and ethanolamine are produced by PEA catabolism; these compounds do not seem to produce significant adverse effects [14]. Clinical protocols seem to confirm the safety of PEA application in real life too. In a recent meta-analysis [15] of 12 studies on the use of micronized and ultra-micronized PEA on chronic and/or neuropathic pain, the authors found PEA to be an effective treatment for pain and registered no serious adverse effects. Moreover, in the work of Bacci et al. [16] regarding the efficacy of PEA in reducing swelling and pain after dental surgery, only two in thirty patients reported adverse events: an episode of tachycardia, which developed about an hour after taking the medication; and an episode of drowsiness after taking the pill. These data seem to confirm that PEA use in in vivo clinical trials is an effective and safe option.

At the same time, an AD-like animal model of Tg2576 mice, aged 10/12 months, had a reduced concentration of PEA and its congener, AEA, when compared to age-matched wild-type littermates. Notably, MCI subjects had reduced plasma levels of PEA compared with age-matched controls. In agreement with these data, the key PEA-hydrolyzing enzyme, FAAH, is significantly up-regulated in peripheral monocytes isolated from AD patients, and its level correlates with the severity of the disease, suggesting that PEA signaling is impaired during AD progression [17].

The main hypothesis of this study is that, as AD is a neurodegenerative disorder with a prominent inflammatory component, AD patients could benefit from the assumption of PEA. To date, the effectiveness of PEA as an adjuvant for the management of cognitive decline in subjects with MCI has not been explored. Therefore, we aim to explore its effectiveness in managing AD-related neuroinflammation and interfering with the progression of the disease through neurodegeneration.

## 2. Materials and Methods

### 2.1. Aims, Design and Setting of the Study

This study has the following specific aims:Aim 1: To determine if PEA has any effect on neuropsychological, behavioral and functional assessment scores after one-year treatment by comparing treated and placebo arms, both in MCI and control groups;Aim 2: To determine if PEA modifies inflammatory and neuronal damage markers, both at the blood and urine levels in MCI subjects;Aim 3: To determine if these changes correlate with clinical scores in all study participants.

This study will be a double-blind placebo-controlled randomized clinical trial, performed on MCI subjects according to Petersen [18] and the International Working Group for people with amnestic MCI criteria [19]. The initial screening of suitable participants with MCI will take place at outpatient-specific facilities of the “Santa Lucia” Neuroscience and Rehabilitation Foundation (Rome).

Aim 1:

During the recruitment period (0–12 months), an evaluation of the demography, history of concomitant diseases, dietary habits, body mass index (BMI), Mini Mental State Examination (MMSE; [20,21]) and Clinical Dementia Rating scale (CDR; [22]) assessment will be performed for screening all participants, according to the cognitive assessment tools most widely used in Italy. Then, all suitable subjects will be enrolled in the project.

At baseline (T0), a full cognitive, behavioral and functional assessment will be performed by administration of the Repeatable Battery for the Assessment of Neuropsychological Status (RBANS; [23]), Hospital Anxiety and Depression Scale (HADS; [24]) and Instrumental Activities of Daily Living (IADL) questionnaires [25]. Then, a dual-task (DT) protocol will be assessed [26].

All subjects will be randomly assigned 1:1, with the use of a numeric sequence standard procedure, into treated-with-PEA (composed of 600 mg PEA in capsules; orally, two times per day) or placebo (capsules; orally, two times per day) arms. Both MCI subjects and controls will be divided into two arms: for the MCI group, 25 subjects will be randomized in the PEA arm and 25 subjects in the placebo arm; for control group, 15 controls will be randomized in the PEA arm and 15 in the placebo arm. At the time of enrollment, all participants will be assigned to one of the two main groups (MCI or HC), then they will be assigned a sequential number. Following the random generation sequencing program (www.randomizer.org), each participant will be automatically assigned to one of the two treatment conditions without the direct involvement of any researcher, in order to avoid any personal bias.

Treatment will last for 12 months (T1), followed by a 6-month observational period (T2). All evaluations performed at T0 will be reassessed at T1 and T2.

Aims 2 and 3:

In addition to the above, blood and urine specimens will be obtained from all participants at T0, T1 and T2. All samples will be immediately stored and then analyzed for measuring PEA, its endocannabinoid congeners and other biological markers.

The planned duration of the study is 36 months considering subject enrollment, clinical evaluation, sample collection, treatment duration, post-treatment follow-up, processing, interpretation and result disclosure.

Figure 1 shows the study flowchart.

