### 2.2. Recruitment and Screening of Participants

Patients will be enrolled in the experimental group according to the following criteria:

Inclusion criteria: aged 60–89 years, possession of the capacity for making decisions, have a reference person (caregiver or companion), be able to read and write in Italian, a MMSE score between 23 and 26.9 points [20,21] and a CDR score < 0.5 [22].

Exclusion criteria: severe physical comorbidity that may limit the execution of the DT protocol, current significant neurological disease (e.g., diagnosis of Dementia, traumatic brain injury, etc.), a current history of alcoholism and/or substance abuse.

A parallel CTRL group of cognitively intact (MMSE score ≥ 27 points [20,21]) age- and sex-matched subjects will be also recruited. Screenings will be conducted by trained physicians and/or neuropsychologists.

We predicted an initial sample of 90 subjects, of which 60 are MCI and 30 CTRL. Then, we hypothesized that the sample size would be reduced due to the inclusion and exclusion criteria (i.e., a worsening in the cognitive functioning corresponding to an MMSE score < 23 points, and a reduced therapeutic adherence, more likely in the MCI group) and possible drop-outs. Therefore, the predicted final sample comprises 80 subjects, of which 50 are MCI and 30 CTRL.

All patients will be informed about the purposes of the research, and all procedures will be carried out with the appropriate understanding and written consent of the subjects, in accordance with the Declaration of Helsinki. Approval of the whole project will be obtained from the Independent Local Ethical Committee.

The inclusion and exclusion criteria are shown in Table 1.

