## 3. Statistics and Outcomes

### 3.1. Data Analysis

The sample size needed to achieve significant differences was determined based on an a priori power analysis, using the software G*Power 3.1 (Version 3.1.9.4; Program written by Franz Faul, Universatat Kiel, Germany) [30] and published data on changes of Aβ42 levels in CSF of MCI vs. CTRL [31]. For a two-sample *t*-test, accepting a probability of type I error of 5% and a probability of type II error of 20%, required the following sample size for the outcome: Aβ 42 (ngl/mL), delta 42, SD 52, results to be N = 25/group. Based on the above, we propose to enroll 30 subjects per group, with the intent of having 23–25 finishers per group to account for potential dropouts. For the aims of our study, we plan to also enroll 30 control subjects that will be equally distributed within the PEA and placebo arms.

Experimental data will be analyzed using Student’s *t*-test or one- and two-way analyses of variance, followed by Bonferroni post hoc test for multiple comparisons. Differences between the groups will be considered statistically significant at values of *p* < 0.05. Pairwise correlation between variables will be assessed via Pearson’s test and confirmed using Spearman’s rank. Significant outliers will be excluded performing the Grubbs’ test, again, with statistically significant values considered at *p* < 0.05.

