### 3.2. Outcomes

For the primary outcome of the study, we expect that PEA administration will decrease the levels of neuroinflammation markers and improve cognitive performance in MCI subjects.

Moreover, for the secondary outcome, we expect to find a reduced conversion from MCI to AD in subjects treated with prolonged PEA administration compared to those within the placebo arm.

For the last outcome, we will also identify the PEA-induced biochemical profile of selected AD targets and its correlation with MCI subjects’ cognitive performance, gaining new insight into biological mechanisms underlying PEA effects on amyloidosis-induced pathology.

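### Aim 3's marker-cognition correlation has two stated populations and only an unadjusted method, so a factor that shifts both variables could pass for an individual-level link

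*Protocol article*

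**What the plan says.** The Protocol article describes the population for this correlation in more than one way.

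- **Section 2.1, Aim 3:** "To determine if these changes correlate with clinical scores in all study participants". The phrase 'these changes' points back to Aim 2, which concerns "inflammatory and neuronal damage markers, both at the blood and urine levels in MCI subjects".
- **Section 3.2, last outcome:** the PEA-induced biochemical profile and "its correlation with MCI subjects’ cognitive performance".
- **Section 3.1, method:** "Pairwise correlation between variables will be assessed via Pearson’s test and confirmed using Spearman’s rank". No grouping factor, stratum or covariate is named.

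The participants form four cells. In section 2.2, "the predicted final sample comprises 80 subjects, of which 50 are MCI and 30 CTRL". In section 2.1, "25 subjects will be randomized in the PEA arm and 25 subjects in the placebo arm", and "15 controls will be randomized in the PEA arm and 15 in the placebo arm". Section 2.2 selects the two diagnostic groups on non-overlapping MMSE ranges: 23 to 26.9 for MCI, and 27 or more for controls.

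**The concern.** A raw correlation over several groups mixes two things: the association among individuals inside a group, and the differences between group means. If one factor shifts both variables, the second part alone makes the coefficient non-zero. Two factors could do so here. Diagnosis separates the groups on cognitive level by selection, and the article also expects marker levels to differ: the Introduction cites lower plasma PEA in MCI, and section 3.1 sizes the trial on an MCI-control difference in Aβ42. PEA is the other: section 3.2 hopes it will lower inflammatory markers and improve cognition in MCI.

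Section 3.2 means to draw mechanistic insight from this correlation. A contrast between diagnoses or arms could then be reported as evidence that a person's marker tracks that person's cognition. Confirmation by Spearman is no check on this, because ranks carry the same group differences.

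**Working it through.** **The plan's own figure.** Section 3.1 gives a difference of 42 and an SD of 52, so d = 42/52 = 0.81. With two-sided 5% and 80% power, the exact t-test solution is 25.06 per group (power 79.9% at 25), which reproduces the stated 25. The article gives no figure for the correlation analysis.

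**Inputs.** The cell sizes 25/25/15/15 come from section 2.1, and 0.81 SD from section 3.1. All other shifts are assumptions. The within-cell correlation is set to zero, so every rejection is a false positive for an individual-level link.

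**Expected coefficient.** If the marker and score means vary between cells with variances Vx and Vy and covariance C (in within-cell SD units), the expected r is about C / √((1 + Vx)(1 + Vy)). With 80 subjects the critical value at two-sided 5% is 1.99 / √(78 + 1.99²) = 0.22.

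1. *Levels; diagnosis shifts the marker by 0.81 SD and cognition by 1.0, 1.5 or 2.0 SD.* The variance of the diagnosis indicator is (50/80)(30/80) = 0.234. For 1.0 SD, r = 0.234 × 0.81 × 1.0 / √((1 + 0.234 × 0.81²)(1 + 0.234 × 1.0²)) = 0.16. For 1.5 and 2.0 SD it is 0.21 and 0.25.
2. *PEA shifts the marker change by 0.81 SD in MCI only; score levels differ by 1.5 SD between diagnoses.* The share of subjects who are MCI on PEA is 25/80 = 0.3125, and its covariance with diagnosis is 0.3125 × 0.375 = 0.117. The variance of that indicator is 0.3125 × 0.6875 = 0.215. So r = 0.117 × 0.81 × 1.5 / √((1 + 0.215 × 0.81²)(1 + 0.234 × 1.5²)) = 0.11.
3. *PEA shifts both change scores by 0.81 SD in MCI only.* r = 0.215 × 0.81² / (1 + 0.215 × 0.81²) = 0.12.

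**Simulated rejection rates** (20,000 runs per scenario, all 80 subjects, nominal 5%):

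| Scenario | Pearson | Spearman |
|---|---|---|
| 1. Levels, marker 0.81 SD, cognition 1.0 / 1.5 / 2.0 SD | 30 / 50 / 65% | 29 / 50 / 65% |
| 2. PEA shifts marker in MCI; score differs by diagnosis | 15.5% | 15.9% |
| 3. PEA shifts both in MCI, 0.81 SD | 19% | 19% |
| Diagnosis shifts both, 0.5 SD | 7.6% | 7.6% |
| Arm shifts both (all subjects), 0.5 SD | 8.0% | 7.7% |
| Marker differs by arm only, score by diagnosis only | 4.3% | 4.2% |

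Adjusting for the four diagnosis-by-arm cells returns about 5% in every scenario.

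**MCI subjects alone.** Restricting to the 50 MCI subjects removes the effect of diagnosis (about 5%). It does not remove a shared effect of arm: a PEA shift of 0.81 SD on both variables still gives 16% if arm is ignored, and 0.5 SD gives 7%.

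**The case against.** **Pooling is not stated.** Aim 3 says whose data are used, not that one coefficient is computed over everyone, and both Aim 2 and section 3.2 point to MCI subjects. This stands as a limit. Pooling remains the natural reading of a pairwise correlation in all participants, and the conflict between sections 2.1 and 3.2 exists on any reading.

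**Covariates for a late-listed aim belong in the analysis plan.** This would dispose of the point if the article were silent. It is not: it names a method and two populations.

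**The large error rates describe a different analysis.** A reader might infer that the planned test is bound to reject far more often than 5%, in the 30-65% range. The documents do not support that. Aim 3 correlates marker changes, and no MCI-control difference in marker change is given. The 0.81 SD is a CSF Aβ42 level difference, while this trial collects blood and urine. The 1-2 SD cognitive gap is assumed, and non-overlapping MMSE ranges at screening do not make RBANS, HADS, IADL or dual-task scores equally separate.

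**Arm differences are not built in.** A reader might also infer that the design itself creates a PEA-placebo difference. It does not: arms are randomised, and a difference is the hypothesis. If PEA moves both variables, that joint movement is part of what section 3.2 asks about. So an unadjusted coefficient is legitimate as a description, but it cannot by itself show an individual-level link.

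**Conclusion.** The point holds in conditional form. Two things are firm: sections 2.1 and 3.2 disagree on the population, and the only method named cannot separate a group or arm contrast from a within-group association.

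The most relevant size is about 15-20% rejection at nominal 5%. It rests on a 0.81 SD PEA effect on the marker change in MCI, together with a 1.5 SD diagnostic difference in score or a 0.81 SD treatment effect on it. The 0.81 is borrowed from the sample-size paragraph and is not an estimate for these markers. Inflation needs a single factor, or linked factors, to shift both variables; it is minor at 0.5 SD and absent otherwise. Adjustment for diagnosis is not in dispute when controls are included. Adjustment for arm depends on the claim being made, and is needed when that claim is about individuals.

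**What to change.** - In sections 2.1 and 3.2, name the same population for Aim 3, with MCI subjects as the main one, as section 3.2 already has it.
- In section 3.1, state that any analysis that includes controls uses partial correlations, or a regression, adjusted for diagnosis group.
- In section 3.1, also state that the arm-adjusted (within-arm) coefficient is the evidence for an individual-level marker-cognition link, and that the unadjusted coefficient is descriptive. If controls are included and PEA may act only in MCI, adjust for the four diagnosis-by-arm cells.

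The cost is about one added sentence in section 3.1 and aligned wording elsewhere, with no new data. Arm adjustment within MCI uses 1 of 48 degrees of freedom. With all 80 subjects, diagnosis uses 1 of 78 and the four cells use 3.

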### 2.2. Recruitment and Screening of Participants

Patients will be enrolled in the experimental group according to the following criteria:

Inclusion criteria: aged 60–89 years, possession of the capacity for making decisions, have a reference person (caregiver or companion), be able to read and write in Italian, a MMSE score between 23 and 26.9 points [20,21] and a CDR score < 0.5 [22].

Exclusion criteria: severe physical comorbidity that may limit the execution of the DT protocol, current significant neurological disease (e.g., diagnosis of Dementia, traumatic brain injury, etc.), a current history of alcoholism and/or substance abuse.

A parallel CTRL group of cognitively intact (MMSE score ≥ 27 points [20,21]) age- and sex-matched subjects will be also recruited. Screenings will be conducted by trained physicians and/or neuropsychologists.

We predicted an initial sample of 90 subjects, of which 60 are MCI and 30 CTRL. Then, we hypothesized that the sample size would be reduced due to the inclusion and exclusion criteria (i.e., a worsening in the cognitive functioning corresponding to an MMSE score < 23 points, and a reduced therapeutic adherence, more likely in the MCI group) and possible drop-outs. Therefore, the predicted final sample comprises 80 subjects, of which 50 are MCI and 30 CTRL.

All patients will be informed about the purposes of the research, and all procedures will be carried out with the appropriate understanding and written consent of the subjects, in accordance with the Declaration of Helsinki. Approval of the whole project will be obtained from the Independent Local Ethical Committee.

The inclusion and exclusion criteria are shown in Table 1.

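### The forecast fall from 60 to 50 MCI subjects relies partly on MMSE decline below 23 and poor adherence; if that removal follows randomisation it selects on outcome-related variables, and the sections conflict on its timing.

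*Protocol article*

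**What the plan says.** All references are to the protocol article.

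- **Section 2.2, starting and final numbers.** "We predicted an initial sample of 90 subjects, of which 60 are MCI and 30 CTRL". After the expected losses: "Therefore, the predicted final sample comprises 80 subjects, of which 50 are MCI and 30 CTRL". All ten losses are in the MCI group.
- **Section 2.2, reasons.** "we hypothesized that the sample size would be reduced due to the inclusion and exclusion criteria", which the text explains as "a worsening in the cognitive functioning corresponding to an MMSE score < 23 points, and a reduced therapeutic adherence". Possible drop-outs are then added as a further reason.
- **Section 2.1, randomisation.** 25 MCI subjects are randomised to PEA and 25 to placebo.
- **Section 3.1, enrolment.** 30 subjects per group are enrolled so that 23–25 per group finish.
- **Section 3.2, outcomes.** The primary outcome pairs neuroinflammation markers with cognitive performance. For the secondary outcome, "we expect to find a reduced conversion from MCI to AD in subjects treated with prolonged PEA administration".
- **Section 2.1, schedule.** MMSE and CDR belong to the recruitment step, whose "assessment will be performed for screening all participants". The T0 battery is RBANS, HADS, IADL and the dual task, and it is the T0 evaluations that are repeated at T1 and T2.

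**The concern.** Two of the stated reasons for shrinking the sample look like events that occur during the trial. A subject cannot adhere poorly to capsules before receiving them. Entry to the MCI group already requires an MMSE of 23 to 26.9, so a worsening to below 23 suggests a change after entry.

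If such subjects are removed after randomisation, the arms that remain are no longer the arms that were randomised. A low follow-up MMSE is related both to cognitive performance and to conversion. A treatment that slows decline keeps more of its own subjects above 23, so the placebo arm loses more of its worst performers and the contrast among those retained shrinks. Subjects likely to convert are also among those removed, and few conversions are expected in the first place. Removal for poor adherence can push the estimate in either direction. The result would not estimate the effect of being assigned to PEA.

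**Working it through.** **1. The plan's own sample size reproduces.** Section 3.1 gives delta 42, SD 52, alpha 5% and power 80%. With n per group = 2 × [SD × (1.960 + 0.842) / delta]², the result is 2 × (52 × 2.802 / 42)² = 24.06, rounded up to 25. The exact two-sided t-test gives 25.06, with power 79.9% at 25. The sample-size arithmetic is not in question here.

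**2. Where the loss falls.**

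| Section | MCI at start | MCI at end | Loss |
|---|---|---|---|
| 2.2 | 60 | 50 | 10/60 = 16.7% |
| 3.1, per group | 30 enrolled | 23–25 finishers | 5/30 to 7/30 = 16.7% to 23.3% |
| 2.1 | 25 + 25 randomised | not stated | – |

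Sections 2.2 and 3.1 agree if 30 per arm are allocated and about 25 finish. Section 2.1 agrees with section 2.2 only if the ten are lost before randomisation, but the adherence ground cannot operate then. No single reading satisfies all three.

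**3. Direction and size of the bias if removal follows randomisation.** The documents give no MMSE change or SD, so these inputs are assumptions: baseline MMSE uniform on 23–26.9, mean placebo decline 0.3 with SD 1.2, correlation 0.6 between MMSE change and RBANS change, and a true benefit of 0.5 SD on both. Everyone whose follow-up MMSE is below 23 is removed, in a simulation with a very large number per arm.

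- Removed: about 16% of placebo and 9% of PEA, averaging about 12.6%. That fits inside the plan's 16.7% loss from all causes.
- Effect among those retained: about 0.45 SD instead of 0.50.

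A second set of assumptions measures the effect on the MMSE itself: mean placebo change −0.5, SD 1.5, true benefit 1.0 point. It removes 22% of placebo and 10% of treated subjects, averaging 16%, and leaves 0.77 of the 1.0 point. With larger assumed declines and SDs (mean change down to −1.5, SD up to 2.5) the retained difference falls as low as 0.55, but removal then reaches 44% and 30%, well beyond the loss the plan expects. The direction is the same in every setting tried; the size is not.

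**4. How few conversions there are to lose.** The Introduction describes MCI "with an annual conversion rate to dementia up to 15% per year". At that upper rate, 25 placebo subjects give 25 × 0.15 = 3.75 expected converters at 12 months and 25 × (1 − 0.85^1.5) = 5.4 at 18 months. At assumed rates of 10% and 5% the 12-month figures are 2.5 and 1.25. Even 0/25 against 5/25 gives a two-sided Fisher p of 0.0502.

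**5. Keeping everyone does not cost planned power.** For the stated delta and SD, the t-test has 86.8% power at 30 per arm, 79.9% at 25 and 76.4% at 23. This assumes that all 30 supply data and that non-adherence does not dilute the effect.

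**The case against.** The strongest reply is that section 2.2 makes a forecast and sets no analysis rule. It speaks of a predicted sample and a hypothesised reduction. Neither worsening nor poor adherence appears in the formal exclusion list or in Table 1. Section 3.1 defines no analysis set, and analysis populations are commonly left to a full protocol or SAP that is not shown. This stands in part: a reader might infer that the protocol orders removal after randomisation, and the text does not go that far. But it names criteria as the cause of the reduction and lists drop-outs separately, so it describes more than ordinary attrition.

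A second reply is that the loss precedes randomisation, with MMSE 23 simply the lower entry limit checked again during the 12-month recruitment period. Section 2.1's 25 + 25 supports this, and for the MMSE ground it is possible. It does not work for adherence, and it sits badly with the finishers in section 3.1. The conflict therefore stands.

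Third, MMSE is not scheduled after screening, so there is no planned measurement on which a follow-up cut-off could act. That is correct. It means that the timing of the cut-off is not fixed, and also that decline on this scale would go unrecorded. RBANS and IADL are repeated and do give cognitive and functional data, but the scales used to classify subjects at entry are not.

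Fourth, the bias is small against the noise. In the mild scenario it is 0.05 SD, against a standard error of √(2/25) = 0.28 SD at 25 per arm. This is fair. The objection to the removal is that it is systematic and avoidable, and that outcomes not collected cannot be recovered later.

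**Conclusion.** The point holds conditionally. Sections 2.1, 2.2 and 3.1 cannot all be followed as written on when MMSE below 23 and poor adherence take effect. If they take effect after randomisation, the comparison is selected on variables related to cognition and conversion. With a working treatment, the MMSE part biases the cognitive effect toward zero, from 0.50 to about 0.45 SD under mild assumptions compatible with the plan's expected loss. The adherence part has no predictable direction.

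Three stronger readings are not supported:

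- **That the converters are deleted.** MMSE below 23 is not AD conversion; likely converters are among those removed, no more than that.
- **That the whole primary outcome is affected in this way.** Cognition is one half of it, beside neuroinflammation markers, and it is assessed with RBANS.
- **That the attenuation is severe.** Assuming a mean decline of 1.5 with SD 2 takes 0.50 to 0.38 SD, but removes about 34% on average, or 0.34 × 60 ≈ 20 subjects. That is twice the ten losses the plan expects from all causes.

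Separately, and with no such condition, MMSE and CDR are listed only at screening, so neither is scheduled at T1 or T2 to record decline or conversion.

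**What to change.** 1. Reconcile sections 2.1, 2.2 and 3.1: state how many MCI subjects are randomised and at what point the expected ten are lost.
2. State that the MMSE limit and the other eligibility criteria apply at screening, before randomisation.
3. Follow every randomised participant to T1 and T2, and analyse each in the assigned arm whatever the later MMSE or adherence. This concerns data collection and analysis, not whether a participant continues treatment.
4. Report an adherent-only analysis as sensitivity.
5. Repeat MMSE and CDR at T1 and T2.
6. Report conversion by arm descriptively, with a confidence interval for the difference.

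The cost is protocol wording, continued visits for participants already enrolled, and two short scales already in use added to two existing visits.
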